### Study population

Patients who meet the following inclusion and none of the exclusion criteria would be eligible for this study and consecutively enrolled in the study.

#### Inclusion criteria

Patients with high-grade glioma (grading criteria, WHO III and IV) after neurosurgical tumor resection or biopsy;Had either postoperative chemotherapy, or radiotherapy, or both at the same time;Age between 18 and 75 years;Willing and able to follow the study intervention, and to comply with the study conditions;Provide signed written informed consent;

#### Exclusion criteria

Severe psychiatric (psychosis, suicidal behavior, substance abuse disorder) issues;Severe and somatic comorbidities (severe cardiovascular disease, severe diabetes, impairments of the musculoskeletal system); severe cardiopulmonary conditions;Withdrawal from the study; either the patient wants to withdraw, or one of the principal investigators determines that due to unfavorable somatic or mental issues the participant is unsuitable for further participation in the study.

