#### Active control condition

For 6 consecutive weeks, participants of the control condition will meet twice per week for 30–45 min but by contrast to the endurance and resistance training condition, the participants would not perform any planned physical exercise. Each session would take place in small groups of 2 to 4 participants. The control condition is not a ‘bona fide’ condition, which would be actually intended to elicit change [26, 27], that is to say, by default, group sessions in psychotherapy follow the aim to change participants’ dysfunctional cognitive-emotional concepts and information processing; By contrast, in the present control condition, topics such as successful coping strategies are not treated and not proactively proposed by the clinical psychologist responsible to monitor the content of the control conditions. Rather, the participants would be encouraged to proposing and exchanging daily life experiences.

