### Statistical analyses

Irrespective of which study conditions the patients are grouped to, at baseline, we will use Pearson’s correlations and univariate ANOVAs to examine the associations between the participants’ social and demographic background and their psychological wellbeing, sleep, QoL, and physical fitness. To examine whether and to what degree the three study conditions (endurance training, resistance training, active control) would impact the outcome variables over time, a series of ANOVAs for repeated measures with the following factors and dependent variables will be performed, namely, time (baseline; week-3 and week 6 since start of study); group (endurance training; resistance training; active control), and the time-by-group interaction; dependent variables: depressive symptoms, anxiety, stress, sleep complaints, QoL, cardiorespiratory fitness, and grip strength. Given the explorative character of the present study, we follow the previously reported recommendations [50, 51] and no correction of p-values for multiple testing would be performed. Data would be analyzed both per protocol and by intent-to-treat (ITT), with the last observation carried forward (LOCF). Patients will not be further followed up as regards the study questions, though, they would undergo routine checks every 6 months to monitor the development and recovery process of the HGG. The level of significance is set at alpha ≤ 0.05. All computations would be performed with the Statistical Package for the Social Sciences (SPSS)^®^ software (IBM Corporation, Armonk NY, USA) for Macintosh^®^.

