### Study harms

After every intervention/session, participants would be investigated for any pain felt or other/additional unpleasant and unexpected sensations, which can be plausibly associated with the study intervention. Adverse events would be listed and discussed if the participant is to be excluded from the study.

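### Withdrawal, including removal by an investigator, is listed as an exclusion criterion and ends study participation with no continued assessment described; harms are filtered by attribution before they are recorded

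*Protocol article*

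**What the plan says.** Under Study population, the exclusion criteria decide who may enter: "Patients who meet the following inclusion and none of the exclusion criteria would be eligible for this study". The list under Exclusion criteria ends with an item of another kind, withdrawal. It covers a patient's own wish to leave and also the judgement of a principal investigator that "due to unfavorable somatic or mental issues the participant is unsuitable for further participation in the study". No arm is named.

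Under Study harms, participants in every arm are questioned after each session about pain or other "unpleasant and unexpected sensations, which can be plausibly associated with the study intervention". The section continues: "Adverse events would be listed and discussed if the participant is to be excluded from the study".

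Under Statistical analyses, the plan is "Data would be analyzed both per protocol and by intent-to-treat (ITT"; the same sentence names LOCF. Under Active control condition, sessions match the exercise arms in number and length, but "the participants would not perform any planned physical exercise". Under Randomization, blinding is stated only for the experts who rate depression.

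**The concern.** Being unsuitable to continue can only arise after enrolment, so it cannot be an eligibility criterion. The item is really a withdrawal rule, and it takes the patient out of the study as a whole. The article does not separate stopping the sessions from stopping the measurements. The patients most likely to be removed are those who are getting worse, and in high-grade glioma during adjuvant treatment that is foreseeable. Their later outcomes are the ones the comparison most needs.

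The harms wording adds to this. Events are tied to exclusion from the study, and the sentence can be read two ways: events are discussed in order to decide on exclusion, or they are listed only when exclusion arises. The enquiry also asks only about sensations "which can be plausibly associated with the study intervention". A judgement on cause is therefore made before anything is recorded, and a patient who is absent because of an event is not reached by an after-session question.

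**Working it through.** **The plan's own figure.** The sample size section gives f = 0.25, alpha 0.05, power 0.80, 3 groups, 3 measurements and N = 36. The correlation between measurements is not stated; I assume 0.5, with sphericity. Then λ = f²·N·m/(1−ρ) = 0.0625 × 36 × 3 / 0.5 = 13.5, with df 4 and 66, and power is 0.823. The smallest N is 35, which is 36 in equal groups, so the figure reproduces. Correlations from 0.3 to 0.7 give N from 48 to 24. The recruitment target of 45 equals 36/(1−0.20), which covers 9 losses, or 3 per arm. The sample size is not at fault here. It shows that losing about 3 of 15 per arm is within what the plan allows for.

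**Illustration of bias (assumed inputs).** There is no true effect and there are 15 patients per arm. Outcomes are in baseline SD units. The mean decline to week 6 is d = 0.5 SD. With correlation 0.5 the SD of change is √(2(1−0.5)) = 1. The k patients with the worst change are removed. Let S_k be the expected sum of the k largest of 15 standard normal values: S₁ = 1.736, S₃ = 3.932, S₄ = 4.646.

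*LOCF from baseline* (a removed patient counts as no change). Bias = [(k_E·d + S_E) − (k_C·d + S_C)]/15, where E is an exercise arm and C is control.
- 3 v 1: [(1.5 + 3.932) − (0.5 + 1.736)]/15 = 3.196/15 = 0.21 SD.
- 4 v 1: [(2.0 + 4.646) − 2.236]/15 = 4.410/15 = 0.29 SD.

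*LOCF from week 3*, if half of the change had already been captured: half of these, 0.11 and 0.15 SD.

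*Per protocol* (removed patients dropped). Bias = S_E/(15−k_E) − S_C/(15−k_C).
- 3 v 1: 3.932/12 − 1.736/14 = 0.328 − 0.124 = 0.20 SD.
- 4 v 1: 4.646/11 − 0.124 = 0.422 − 0.124 = 0.30 SD.

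A simulation of the same set-up agrees to within 0.002 SD.

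**Range.**
- Equal removal (3 v 3): the terms cancel and the between-arm bias is zero.
- No average decline (d = 0): LOCF gives (3.932 − 1.736)/15 = 0.15 and (4.646 − 1.736)/15 = 0.19 SD from baseline, and half of these (0.07 and 0.10) from week 3. The per-protocol results do not change.
- A cruder assumption, that removed patients simply change 1 SD worse than those who stay, gives 4/15 − 1/15 = 0.20 SD per protocol.
- All randomised patients assessed at week 6: this source of bias is zero.

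**Scale.** The standard error of a difference in mean change between two arms of 15 is √(2/15) = 0.37 SD. The LOCF biases with d = 0.5 are therefore about 0.3 to 0.8 of a standard error (0.11/0.37 to 0.29/0.37).

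**The case against.** The strongest reply is that this is a withdrawal rule under the wrong heading and little more. Much of that stands, and several stronger readings that a reader might infer are not supported.

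- *That the rule contradicts the ITT analysis, or makes randomised patients ineligible after the fact.* It does not. LOCF presupposes that some patients leave and keeps them in the ITT set, and the target of 45 allows for drop-outs. Table 1 places the eligibility check once, at week −1. Nothing says that a randomised patient is deleted from analysis.
- *That patients leave more easily from the exercise arms.* The wording is arm-neutral and no drop-out rate by arm is given. Endurance participants may adjust their pace and pause. Unequal removal is a risk: intervention-related discomfort is likelier with treadmill or resistance work than with conversation. It is not a documented fact.
- *That unblinded investigators decide.* The article does not say whether those deciding know the allocation. It keeps one principal investigator out of assessment and randomisation.
- *That control-arm events go largely unrecorded.* The enquiry follows sessions in all arms, and adverse events are not among the dependent variables, so no planned between-arm test is spoiled. The documents give no basis for sizing this part.

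It can also be said that the loss of later measurements is inferred, since the participant timeline has patients reassessed after weeks 3 and 6 and nowhere says this stops. But the rule ends participation in the study, the article describes no exception, and LOCF is the planned substitute for missing values. Condensing a full protocol into an article explains omissions; it does not explain a rule that is stated and misplaced, or a harm enquiry that is stated with an attribution filter.

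**Conclusion.** The point holds in this form. A post-enrolment removal rule sits in the eligibility list, it ends participation in the study rather than in the sessions, and adverse events are tied to it. Keeping removed patients in the ITT set does not cure the problem, because LOCF supplies a value from before the deterioration; the per-protocol analysis may lose these patients altogether.

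The size depends on inputs the article does not give. It rests on the worst decliners being the ones removed, on 3 v 1 or 4 v 1 removals of 15, and on a correlation of 0.5. Removing exactly the worst decliners is a strong form of selection. On those terms the spurious advantage for exercise is about 0.1 to 0.3 SD under LOCF and 0.2 to 0.3 SD per protocol. It is less than one standard error, but systematic. With equal removal it is about zero. The harms wording is a separate defect of recording, with no size attached. The change should be made, and the sections on study population, exclusion criteria, harms and analysis should be reconciled.

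**What to change.** 1. Take withdrawal out of the exclusion criteria and give it its own section.
2. In that section, separate stopping the sessions from leaving the study. The clinical decision to stop sessions is left as it is.
3. Keep the scheduled week-3 and week-6 assessments for every randomised patient who still consents, whether or not sessions continue, and analyse the observed values in the ITT set. Values still missing because consent is withdrawn remain exposed to the weakness of LOCF.
4. Report removals and their reasons by arm.
5. Record all adverse events in all three arms, at sessions and at weeks 3 and 6, with the judgement on attribution in a separate field. Reword the sentence that ties adverse events to exclusion.

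The cost is amendment wording and a small effort to assess patients who have stopped attending. The visits are already planned, and the sample size does not change.

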### Recruitment

The neurosurgeon (DC; 18 years of experience) is responsible for the recruitment of eligible participants.

### Participant timeline

As shown in Table 1, patients from the Department of Neurosurgery of the Basel University Hospital (Basel, Switzerland) have the following timeline: After neurosurgical treatment of the HGG, the patients would undergo either chemotherapy, or radiotherapy, or both. In parallel, they would be informed about the study content and the study aims. Once the written informed consent is signed, and the baseline assessment (cardiovascular performance and grip strengths; psychological assessments) (Table 1) is completed, the patients will be randomly assigned to one of the three study conditions. For the next 6 consecutive weeks, she/he would follow the schedule with two sessions per week. After the 3rd and 6th weeks, from the start of the study, the patients would be reassessed; similar as to the baseline assessments.

### Sample size calculation

We rely on two approaches: First, for pilot studies and clinical trials, Julious [24] recommended to recruit at least 12 participants/group. Second, we performed a power analysis with G*Power [25] with the following statistical preconditions: Cohen’s f for ANOVAs with repeated measures and within and between interactions: 0.25; alpha: 0.05; Power: 0.8; number of groups: 3, number of measurements: 3; calculated total sample size: 36. To counterbalance possible drop-outs, the sample size was set at 45 participants; 15 participants per group.

### Randomization

The randomizations are to be performed using an online software from the website Randomization.com (http://www.randomization.com). The online generator randomizes each subject to a single treatment using a method of randomly permuted blocks, with random block sizes for sex. Based on the generated list, a psychologist, not involved in the study, prepares 45 sealed envelopes, with no further identification, to be kept in an opaque and closed ballot box which are to be stirred before picking. Next, the psychologist would draw an envelope from the ballot and assign the study participants to one of the three study conditions picked. Once an envelope is drawn, it would be put aside. Experts rating the participants’ depression severity would be blinded to the participants’ study condition assigned.

### Interventions

#### Endurance training

The endurance training will last for 6 consecutive weeks and consists of 2 weekly sessions (30–45 min each). Sessions would take place in small groups of 2 to 4 participants. After 5 min of warming-up and stretching, participants will exercise for 25–35 min on the treadmill at a pace of 11 to 14 points on the Borg Scale of ranging from 0 (complete rest or resting pace) to 20 (maximum pace), followed by 5 min of cooling down. In this study, cooling down represents light exercise to allow the body to gradually transition to a resting or near-resting state. Participants are allowed to adapt to their pace and to take breaks throughout the session, though they are also encouraged to keep both their speed and pace as long as possible.

#### Resistance training

The resistance training will also last for 6 weeks with 2 weekly training sessions (30–45 min each), in small groups of 2 to 4 participants. After 5 min of warming-up, participants will follow a structured and standardized resistance training protocol to strengthen all main bodily skeletal muscles (upper and lower arms; shoulders, upper and lower legs; abdominal muscles; core muscles). The protocol is as follows: The participants would perform each exercise in 3–5 series of 10–15 repetitions per series, at 11 to 15 points on the Borg Scale, followed by the cooling down period. Intervals between the series of 10–15 repetitions will last for about 1–3 min.

#### Active control condition

For 6 consecutive weeks, participants of the control condition will meet twice per week for 30–45 min but by contrast to the endurance and resistance training condition, the participants would not perform any planned physical exercise. Each session would take place in small groups of 2 to 4 participants. The control condition is not a ‘bona fide’ condition, which would be actually intended to elicit change [26, 27], that is to say, by default, group sessions in psychotherapy follow the aim to change participants’ dysfunctional cognitive-emotional concepts and information processing; By contrast, in the present control condition, topics such as successful coping strategies are not treated and not proactively proposed by the clinical psychologist responsible to monitor the content of the control conditions. Rather, the participants would be encouraged to proposing and exchanging daily life experiences.

### Measures

#### Sociodemographic information

At baseline, the participants’ sex, age, civil status, highest educational level, and current job position will be assessed via a self-report.

#### Clinical- and glioma-related information

At baseline, clinical- and glioma-related information such as relevant past medical history, symptoms at initial presentation, neurosurgical procedure, histopathological diagnosis, and genetic subtype of the tumor would be retrieved from the participants’ medical records.

#### Psychological wellbeing

A set of self-report questionnaires will be used to assess the patients’ psychological wellbeing, including symptoms of depression, state- and trait-anxiety, and perceived stress. All questionnaires will be completed at baseline, 3 weeks into the study, and at the end of the study.

#### Depression

As in previous studies [28, 29], participants will complete the Beck Depression Inventory [30] to self-report symptoms of depression. The questionnaire consists of 21 items regarding typical dimensions of depression such as depressive mood, loss of appetite, sleep disorders, suicidality and similar. Answers are given on 4-point-Likert scales with the anchor points 0 (‘as always’; ‘no change’) to 3 (‘not able anymore’; ‘dramatic change’), with higher scores reflecting an increased severity of depressive symptoms. Evidence for the validity of the BDI has been previously reported [30].

#### State and trait anxiety

To assess state-and trait-anxiety, the State–Trait Anxiety Inventory (STAI) [31, 32] will be employed. The STAI consists of 42 items. Typical items for an anxiety state are “I feel relaxed”; “I feel nervous”, or “I feel tensed”. Typical items for anxiety traits are “I get nervous and restless when thinking at all my duties and issues”; “I can’t stop ruminating about unimportant stuff”. Answers would be given on an 8-points rating scale with the anchor points 0 (not true at all) to 7 (completely true), and with higher sum scores reflecting higher state and trait of anxiety. The STAI has been previously proved to have good psychometric properties in previous studies [31, 32].

#### Perceived stress

As previously described [33], we will employ the Perceived Stress Scale (PSS) [34], which has been proved to be a valid instrument in previous research [35], to assess subjectively perceived stress. The questionnaire consists of 10 items and is used to determine perceived overall stress occurring over the previous month. Answers are to be given on five-point rating scales ranging from 1 (never) to 5 (very often), with higher scores reflecting greater perceived stress.

#### Sleep

To assess subjective sleep complaints, participants will complete the Insomnia Severity Index [36, 37], comprising of seven items, answering on a 5-point rating scales (0, not at all, 4, very much), referring to the difficulty in falling asleep, difficulties in maintaining sleep, increased daytime sleepiness, and worriedness about sleep. The higher the overall score, the greater the respondent is assumed to suffer from insomnia. The validity of the ISI has been previously described [36, 37].

#### Quality of life (QoL, SF-36)

As previously described [38, 39], the short form 36 health survey (SF-36) [40] will be employed to assess the participants’ health-related QoL. This self-rating questionnaire consists of eight scales to assess impairments in physical activities (i.e., bathing, dressing, grocery shopping, using stairs, and using escalators) due to health problems (physical functioning), impairments in routine role activities at work or in other daily activities due to physical health problems (role limitations due to physical health), bodily pain, general health perceptions, energy and fatigue (vitality), impairments in social activities due to physical or emotional problems (social functioning), impairments in daily role activities at work or other everyday activities due to emotional problems (role limitations due to emotional problems), and general mental health. Answers would be given on different scales with different anchor points; interim scores would be transformed to achieve a range between 0 (worst QoL) and 100 (best QoL); thus, higher scores reflect a higher self-perceived quality of life. The validity of the SF-36 has been documented in previous research [41].

#### Physical fitness

To assess physical fitness, all participants will perform the 6-min walking test (6MWT) and handgrip strength test at baseline and at the end of the study.

We will use the 6MWT as a measure of cardiorespiratory fitness [42]. The 6MWT is a standardized, self-paced, submaximal exercise test, and has been designed especially for patients suffering from chronic diseases. Evidence of the validity of the 6MWT has been previously shown in various disease types [43–45] including cancer patients [46, 47]. The walking distance will be used as the main outcome measure of the 6MWT. Oxygen saturation before and after the 6MWT will be also taken into consideration.

As a measure of upper body strength, we will perform the grip strength test. As described elsewhere [48], maximum isometric grip force of the dominant hand would be assessed using a mechanic hand dynamometer (Jamar Handgrip Dynamometer; retailer: Rehaforum MEDICAL GmbH; Elmshorn, Germany). Participants will have three attempts per hand. The validity of the grip strength test has been previously documented, and researchers have shown that grip strength is associated with psychological wellbeing across different populations [49].

### Statistical analyses

Irrespective of which study conditions the patients are grouped to, at baseline, we will use Pearson’s correlations and univariate ANOVAs to examine the associations between the participants’ social and demographic background and their psychological wellbeing, sleep, QoL, and physical fitness. To examine whether and to what degree the three study conditions (endurance training, resistance training, active control) would impact the outcome variables over time, a series of ANOVAs for repeated measures with the following factors and dependent variables will be performed, namely, time (baseline; week-3 and week 6 since start of study); group (endurance training; resistance training; active control), and the time-by-group interaction; dependent variables: depressive symptoms, anxiety, stress, sleep complaints, QoL, cardiorespiratory fitness, and grip strength. Given the explorative character of the present study, we follow the previously reported recommendations [50, 51] and no correction of p-values for multiple testing would be performed. Data would be analyzed both per protocol and by intent-to-treat (ITT), with the last observation carried forward (LOCF). Patients will not be further followed up as regards the study questions, though, they would undergo routine checks every 6 months to monitor the development and recovery process of the HGG. The level of significance is set at alpha ≤ 0.05. All computations would be performed with the Statistical Package for the Social Sciences (SPSS)^®^ software (IBM Corporation, Armonk NY, USA) for Macintosh^®^.

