The underlying rationales and research findings are as follows: On a physiological level, some scholars emphasize that regular exercise training has the potential to increase the levels of serotonin, brain-derived neurotrophic factor (BDNF) and endothelial growth factor (VEGF) [7], and to increase mitochondrial activity [8]. On the psychological level, other scholars argue that exercise training has the potential to improve the patients’ mood [9, 10] and self-esteem [11], to decrease symptoms of depression [12–17], anxiety, chronic pain [18], and above all rumination [19]. Further, in a previous study on the post-treatment of patients with post-aneurysmal subarachnoid hemorrhage, we have shown that compared to a control group, a 12-week regular endurance and resistance training ameliorated the symptoms of depression, insomnia and cognitive capacities [20–22]. Next, as regards to cancer survivors, most studies focused on breast cancer survivors during or after treatment [1]. Segal et al. [23] further emphasized that physical activity and exercise interventions were safe, provided benefit in quality of life, and might have the potential to enhance social exchange. In this respect, Brand et al. [19] showed that a single session of exercise could increase interest in social contact and interactions, at least among their investigated 129 inpatients (mean age: 38.16 years; median: 36.00 years; age range: 19–63 years) with a broad variety of psychiatric disorders. However, in regards to patients with HGG, to the best of our knowledge, there has been no study to investigate the impact of exercising on the patients’ well-being and QoL, despite it is well-acknowledged that individuals with HGG who underwent radiotherapy, chemotherapy, or both radio- and chemotherapy suffer from a dramatically decreased in QoL. Accordingly, the primary aim of the present study is to examine and compare the effects of two different types of exercise training (endurance vs. resistance) on psychological wellbeing (i.e., depression, stress, anxiety), sleep, QoL and physical fitness in patients with HGG who had neurosurgery followed by radiotherapy, chemotherapy, or both, compared to an active control condition.

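### The repeated-measures ANOVA treats baseline as an outcome and tests a 4-df interaction with no named contrast; it is valid, but inefficient and poorly matched to the pairwise aim

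*Protocol article*

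**What the plan says.** The Statistical analyses section fixes one model for all outcomes, with factors "time (baseline; week-3 and week 6 since start of study); group (endurance training; resistance training; active control), and the time-by-group interaction". It has no covariate and singles out no comparison between arms. It waives correction for multiple testing.

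The Background gives the primary aim as to "examine and compare the effects of two different types of exercise training (endurance vs. resistance") with an active control as comparator. The Discussion repeats that the two interventions are set against each other, and the section on anticipated outcome expects both exercise arms to improve more than control.

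The Sample size calculation powers the interaction only. It takes Cohen's f "for ANOVAs with repeated measures and within and between interactions: 0.25", with "alpha: 0.05; Power: 0.8; number of groups: 3, number of measurements: 3; calculated total sample size: 36". It then says: "To counterbalance possible drop-outs, the sample size was set at 45 participants; 15 participants per group".

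The Randomization section describes "using a method of randomly permuted blocks, with random block sizes for sex", after which all 45 unmarked envelopes are mixed in one box.

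**The concern.** The planned test and the stated question do not match. The aim contains three pairwise questions. The planned interaction asks one diffuse question: do the three group profiles differ in any way over three visits? A significant answer does not say which training works or whether the two differ. A non-significant one can hide a real difference between two arms.

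The plan also treats baseline, which the intervention cannot affect, as a response. The interaction then works on within-patient changes. Regressing the later value on baseline would use the same data more efficiently in a randomised trial. With 45 patients, that precision matters.

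Finally, f = 0.25 conveys little about a difference between two arms, so a reader of the Sample size calculation cannot tell how large an effect each comparison needs.

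**Working it through.** **Inputs from the documents.** f = 0.25, alpha 0.05, power 0.80, 3 groups, 3 measurements, total 36, recruited 45 (15 per arm). 36/45 = 0.80, so the unstated drop-out allowance is 20%.

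**Assumptions, not in the documents.** Within-patient correlation rho (0.3, 0.5, 0.7), compound symmetry and sphericity, and the time course of the effect. SD means the outcome SD at a single visit.

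**1. Reproducing 36.** Noncentral F with lambda = f²·N·m/(1−rho), df (3−1)(3−1) = 4 and 2(N−3). At rho 0.5:
- N = 36: lambda = 0.0625·36·3/0.5 = 13.5, df 4 and 66, power 82.3%.
- N = 33, the next smaller balanced total: 78.1%.
- N = 45: lambda = 16.875, power 91.1%.

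So 36 reproduces at rho 0.5. At rho 0.3 the requirement would be 48, and at rho 0.7 it would be 24.

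**2. What f = 0.25 means as a week-6 difference D.** f is the root mean square of the nine interaction cell deviations. Their sum of squares is the product of the sums of squared group and time deviations.
- Both exercise arms, linear (0, D/2, D): (6/9)(1/2)D² = D²/3. RMS = D/5.196, so D = 1.30 SD.
- Both arms, full effect by week 3 (0, D, D): (6/9)(6/9)D² = 4D²/9. RMS = 0.2222D, so D = 1.125 SD.
- Graded and linear (endurance D, resistance D/2, control 0): (1/2)(1/2)D² = D²/4. RMS = D/6, so D = 1.50 SD.

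**3. Baseline adjustment against change score, same week-6 contrast.** Change variance is 2(1−rho) and adjusted variance is 1−rho². The ratio is (1+rho)/2, that is 0.65, 0.75 and 0.85 at rho 0.3, 0.5 and 0.7. At 0.75 the equivalent is 1/0.75 = 1.33 times the patients.

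**4. Power for D = 1.0 SD in both exercise arms, uncorrected.** Omnibus lambda = n·(sum of squares)/(1−rho); for n = 15 and rho 0.5 this is 15·(1/3)/0.5 = 10 (linear) or 15·(4/9)/0.5 = 13.33 (early). The contrasts use noncentral t with the pooled three-arm error. For the adjusted contrast with n = 15 and rho 0.5, SE = √0.75·√(2/15) = 0.316 and the noncentrality is 3.16 on 41 df.

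| rho | n per arm | Omnibus, linear | Omnibus, full by week 3 | Change contrast | Adjusted contrast |
|---|---|---|---|---|---|
| 0.5 | 12 | 57% | 71% | 66% | 78% |
| 0.5 | 15 | 69% | 82% | 76% | 87% |
| 0.7 | 12 | 82% | 92% | 87% | 91% |
| 0.7 | 15 | 91% | 97% | 93% | 96% |

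**5. Alpha split over three contrasts (0.05/3), rho 0.5.** Adjusted contrast: 62% (12 per arm) and 74% (15 per arm). At 15 per arm that is ahead of the linear omnibus (69%) but behind the early-effect omnibus (82%).

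**6. Endurance against resistance.** Under the graded pattern at f = 0.25, these arms differ by 1.50/2 = 0.75 SD. At 15 per arm and rho 0.5 the adjusted contrast has 63.9% power, while the omnibus shows 91.1%.

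**7. Difference detectable with 80% power per adjusted contrast, rho 0.5.** About 1.02 SD with 12 per arm and 0.91 SD with 15 per arm.

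**The case against.** The ANOVA is a legitimate analysis of a randomised trial and is the test that the sample size was built on. The Statistical analyses section asks about impact over time, which an interaction addresses, and calls the study explorative. A condensed article may leave follow-up comparisons to an analysis plan that is not shown. All of this stands, and it limits the point to efficiency and focus: the model itself, with baseline as an outcome level and no covariate, is fixed in the text.

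A reader might infer three stronger things that the documents do not support.

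- **That the ANOVA is invalid or underpowered on its own terms.** It is not. 36 reproduces at rho 0.5, and 45 patients give about 91% power at f = 0.25.
- **That the adjusted contrast always has more power than the omnibus.** The comparison depends on time course, rho and multiplicity, and the documents give neither rho nor a time course. At rho 0.7 with full effect by week 3 the omnibus is marginally ahead, and splitting alpha reverses the order at rho 0.5 with an early effect. The plan waives correction, so the uncorrected comparison is the one that applies, but part of the gain comes from testing three contrasts each at 0.05. A week-6 contrast would also miss an effect present only at week 3.
- **That a stratification factor, sex, is left out of the model.** The wording on sex in the Randomization section is loose, and mixing unmarked envelopes in one box could undo stratified blocks. Whether allocation is stratified is therefore unclear. No sex effect is given, so no gain from adjusting for it can be computed.

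The low power for endurance against resistance is not an advantage of the proposed model. It does show that 91% omnibus power says little about a comparison named in the aim.

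**Conclusion.** The point holds as a recommendation on efficiency and focus. Baseline adjustment beats a change score for the same week-6 contrast at every rho below 1 under compound symmetry, apart from one lost degree of freedom; the variance factor is 0.65 to 0.85 over the assumed range. Against the omnibus test, the uncorrected gain at rho 0.5 with 15 per arm and a 1.0 SD effect in both exercise arms is about 18 points for a linear course (87% against 69%) and 5 points for an effect complete by week 3 (87% against 82%). It vanishes at rho 0.7 with an early full effect. Even where power is equal, only named contrasts say which arm differs from which and by how much.

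**What to change.** In Statistical analyses, take weeks 3 and 6 as outcomes in a model with baseline value, group, visit and group-by-visit. Pre-specify three week-6 estimates with 95% intervals: endurance against control, resistance against control, and endurance against resistance.

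In the Sample size calculation, state the rho assumed. Say that f = 0.25 corresponds to a week-6 difference of about 1.1 to 1.5 SD depending on pattern, and that each adjusted contrast has 80% power for about 1.02 SD (12 per arm) or 0.91 SD (15 per arm) at rho 0.5, uncorrected.

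Clarify in Randomization whether allocation is stratified by sex, and add sex to the model only if it is.

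The cost is wording, since baseline and sex are already collected. The detectable difference will look large. The focus on week 6 is also a choice that the investigators must confirm: it is the end of the intervention, but the article names no decisive visit.
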